### Statistical analysis

Data will be analyzed on an intention-to-treat basis. To examine the effects of the intervention on the primary and secondary outcomes, we will conduct multilevel analyses (mixed modeling), taking missing data into account [75]. Depending on the fit of the models, up to four hierarchical levels will be distinguished: outcomes (level 1), nested within children (level 2), nested within therapists (level 3), nested within healthcare centers (level 4). Random intercepts at the subject level, therapist level and healthcare center level will be included only if the Likelihood Ratio Test shows a significant improvement of the model fit. Time will be included as short-term (T1) and longer-term (T2, T3) within-subjects factors and condition (brief parent training vs. CAU) as between-subjects factor. The interaction between time and condition will be examined to interpret changes over time between conditions. To examine whether the candidate moderator variables moderate the intervention effects, these variables will also be added as interaction effects to the multilevel analyses.

To assess the cost-effectiveness of the brief behavioral parent training compared to CAU, we will calculate the Incremental Cost Effectiveness Ratio (ICER) from a societal perspective. We will perform both a cost-utility analysis (based on QALYs) and cost-effectiveness analyses (based on the daily ratings of behavioral difficulties and based on ECBI-I scores). An ICER is calculated by dividing the difference in the total costs by the difference in the total effect (either QALYs or the daily ratings of behavioral difficulties and ECBI-I scores, respectively). In these analyses, the costs of healthcare will be used and interpolated to the previous 12 months. We will compare each ICER based on relevant willingness to pay thresholds. Bootstrapping will be used to calculate the reliability of our estimates.

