### Procedure

Parents in the brief behavioral parent training arm receive three sessions of behavioral parent training. The first two sessions take 120 min each and are planned one or two weeks apart. The third session takes 60 min and is planned one week after the second session. To take parents’ and therapists’ availability into account, some flexibility in planning is allowed as long as all three sessions are planned within six weeks with at least one week between two consecutive sessions. After the third session, parents wishing to receive additional support can receive CAU and/or booster sessions. The booster sessions take 60 min each and can be provided maximally once every four weeks up to one year after the last session of the brief behavioral parent training program. Booster sessions can be suggested by the therapist who provided the brief behavioral parent training or by other involved clinicians, or requested by parents themselves.

The trial contains four measurement occasions, see Fig. 1 for the participant timeline. T0 takes place after parents provide consent and are found eligible for participation, before randomization. The first posttreatment measurement (T1) takes place one week after the third session for parents in the brief behavioral parent training arm and eight weeks after T0 for parents in the CAU arm. The second posttreatment measurement (T2) takes place six months after T1 and the third posttreatment measurement (T3) takes place twelve months after T1. Participation in the trial therefore takes approximately 14 months in total. The care families receive at the child mental healthcare center may terminate sooner if they do not need or want care anymore.

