### Sample size calculation

Based on our previous study that found medium-sized short term effects on daily ratings of behavioral difficulties compared to waitlist (range of Cohen’s *d* = 0.35 to *d* = 0.66, [33]) and studies showing medium-sized parenting intervention effects on behavioral difficulties using parent-report rating scales [19, 20, 25, 36, 72], we estimate the effect of our brief behavioral parent training program as compared to CAU to be at least small (*d* = 0.25).

A power analysis has been performed using G*Power software [73]. Based on an effect size of *d* = 0.25 (*f* = 0.125), two groups and three repeated measures (T0, T1, T2 for short term effectiveness), with *r* = 0.60 between-measurement relation, a power of 0.80 and α = 0.05, we need at least 42 participants per group, resulting in a total of 84 participants. Given that the data are clustered, we increased the sample size with 10% [74], resulting in a total of 93 participants. This is in line with the number of participants in similar studies comparing behavioral treatments to CAU (e.g., [36]).

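### The only within-child dependence named is a random intercept, so if correlation falls over 14 months, T1 would be tested too strictly and T3 too leniently

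*Protocol article*

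**What the plan says.** The Statistical analysis section of the protocol article plans a multilevel model for the primary and secondary outcomes: "Depending on the fit of the models, up to four hierarchical levels will be distinguished", namely outcomes, children, therapists and centres. On the random part it says that "Random intercepts at the subject level, therapist level and healthcare center level will be included", subject to a condition whose full wording is "healthcare center level will be included only if the Likelihood Ratio Test shows a significant improvement of the model fit". No other random term is named, and the covariance of the level-1 residuals is not stated.

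On the fixed part: "Time will be included as short-term (T1) and longer-term (T2, T3) within-subjects factors", and "The interaction between time and condition will be examined to interpret changes over time between conditions". Whether T1 and the later visits share one model is not stated.

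Under Procedure, T1 falls one week after the third session (training arm) or eight weeks after T0 (care as usual), T2 six months after T1, and "the third posttreatment measurement (T3) takes place twelve months after T1". T0 to T3 is therefore about 14 months. The Sample size calculation uses a single correlation for all pairs of visits: "0.60 between-measurement relation, a power of 0.80".

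**The concern.** A subject random intercept with independent, equal-variance residuals is compound symmetry. Every visit has the same variance, and T0 is as strongly correlated with T3 as with T1. The likelihood ratio rule only adds or drops intercepts, and the fit clause concerns the number of levels. Neither adds flexibility within a child.

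A single correlation is open to doubt here for reasons within the protocol. The gaps from T0 run from about 8 weeks to about 14 months. After T1 the training arm may add usual care and booster sessions, and usual care is unrestricted throughout, so families can diverge. Equal variance is also uncertain: targets are chosen because they occur daily at baseline, and a behaviour that later does not occur scores 0. The direction of that second effect is unclear.

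The condition-by-time contrasts carry the first objective, short- and longer-term effectiveness. A model that pools one residual variance over unequal correlations costs power at the short-term contrast and makes the one-year contrast reject too easily.

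**Working it through.** **The plan's own figure.** Repeated-measures within-between interaction with f = 0.125, 2 groups, 3 occasions, r = 0.60, α = 0.05 and N = 84:
- λ = f²·N·m/(1 − r) = 0.015625 × 84 × 3 / 0.40 = 9.84, with df 2 and 164.
- Power is 0.801 (N = 82 gives 0.791), so 84 reproduces. 84 × 1.1 = 92.4, rounded up to 93.
- This calculation assumes the same r for every pair of visits.

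**Formulas for the contrasts** (unit SD, complete data, 47 v 46 families, T0 to T3 in one model):
- k = 1/47 + 1/46 = 0.0430
- SE from the random-intercept model, the same for every visit: √(2(1 − r̄)k), where r̄ is the mean of the six pairwise correlations
- True SE of the (Tk − T0) contrast between arms: √(2(1 − r₀ₖ)k)
- Ratio, model to true: √((1 − r̄)/(1 − r₀ₖ))
- Two-sided type I error: 2[1 − Φ(1.96 × ratio)]

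**Assumed correlations.** The documents give no decay pattern. Two patterns were set so that the six pairs (01, 02, 03, 12, 13, 23) average the plan's 0.60:
- Stronger decay: 0.70, 0.55, 0.45, 0.65, 0.55, 0.70; sum 3.60, mean 0.60
- Milder decay: 0.65, 0.58, 0.52, 0.63, 0.58, 0.64; sum 3.60, mean 0.60

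The model SE is √(2 × 0.40 × 0.0430) = 0.186 in every case.

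| Pattern | Contrast | True SE | Ratio | Type I error |
|---|---|---|---|---|
| Constant 0.60 | T1, T2, T3 | 0.186 | 1.00 | 5.0% |
| Milder | T1 | 0.174 | √(0.40/0.35) = 1.07 | 3.6% |
| Milder | T3 | 0.203 | √(0.40/0.48) = 0.91 | 7.4% |
| Stronger | T1 | 0.161 | √(0.40/0.30) = 1.15 | 2.4% |
| Stronger | T3 | 0.218 | √(0.40/0.55) = 0.85 | 9.5% |

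**Simulation check.** With 40,000 trials per pattern (93 families, complete data), the stronger pattern gave 2.5% at T1 and 9.5% at T3, the milder pattern 3.6% and 7.4%, and a constant correlation 5%. Giving each contrast its own variance restored about 5% in every case. In a separate simulation of 1,500 trials, the correlation fell linearly from 0.70 to 0.50 and 8% dropped out per visit. Type I error was 2.6% at T1 and 7.5% at T3, so moderate dropout does not remove the effect.

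**If the longer-term visits are modelled apart from T1.** A T0/T1 model has only one correlation, so the T1 error disappears. A T0/T2/T3 model still pools three:
- Stronger: r̄ = (0.55 + 0.45 + 0.70)/3 = 0.567; T3 ratio √(0.433/0.55) = 0.89; type I error 8.2%
- Milder: r̄ = (0.58 + 0.52 + 0.64)/3 = 0.58; T3 ratio √(0.42/0.48) = 0.94; type I error 6.7%

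**The case against.** The strongest reply is that the article never limits the model to random intercepts. The word only in that sentence belongs to the likelihood ratio condition. The level-1 covariance is simply unstated, so an autoregressive or heterogeneous residual could still be meant, and a condensed article may leave this to an analysis plan. That stands as a limit on wording. A reader might infer that the protocol fixes a model that gives wrong standard errors, and the text does not go that far. It does, however, state which random terms enter and by what rule, and the ordinary reading of such a model is independent residuals. The point is therefore about the structure described, and an analysis plan that sets another structure would settle it.

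Second, nothing in the documents shows decay. The only figure is a single r = 0.60, and under it every standard error is right. This stands, and the error rates are conditional.

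Third, the plan's 0.60 refers to T0, T1 and T2, whereas the patterns above average 0.60 over six pairs including T3. Over the plan's three pairs they average 0.633 and 0.62. This stands too: the sizes illustrate and do not estimate.

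Fourth, the article does not say that separate contrasts with T0 are the test, nor that one model holds all visits. If T1 is fitted with T0 alone, the short-term part drops out and the longer-term part remains.

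**Conclusion.** The concern holds in conditional form. The random part that the article describes, read in the usual way, allows one variance and one correlation from 8 weeks to 14 months. If correlation falls with time and all visits share a model, the T1 contrast is conservative (type I error about 2.5 to 3.6%) and the T3 contrast anti-conservative (about 7.4 to 9.5%). Fitted without T1, the T3 figure is about 6.7 to 8.2%. With constant correlation and variance there is no error. These sizes rest on assumed correlations, equal variances and independent level-1 residuals. The documents do not support saying that the one-year test will reject too often, only that the described model gives no protection if correlation decays. The change is worth making because it is cheap and makes the test valid in either case.

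**What to change.** State in the analysis section (or analysis plan) that T0, T1, T2 and T3 are modelled as four fixed visits with an unstructured within-child covariance, which replaces the subject random intercept. Keep the therapist and centre terms. Use Kenward-Roger degrees of freedom, and name in advance a simpler fallback if the model does not converge, for example heterogeneous Toeplitz and then heterogeneous autoregressive. Say also whether the short- and longer-term effects come from one model. If an existing analysis plan already sets the covariance, a reference to it is enough.

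The cost is a change of wording before outcomes are analysed, with no new data or recruitment. The within-child part has 10 covariance parameters instead of 2, eight more, and carries some convergence risk with 93 families and missing visits, which is why the fallback should be fixed beforehand.

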### Study setting

To ensure our findings reflect the real-world impact of brief behavioral parent training (i.e., to test effectiveness rather than efficacy), the trial is fully embedded in routine mental healthcare. The participating centers are academic and non-academic youth mental healthcare centers of various sizes. Therapists who provide the brief behavioral parent training have a master’s degree in psychology or child, family and education studies and have had postmaster education in cognitive behavioral therapy (at least 50 h) or have a registered higher vocational education degree as social worker in cognitive behavioral therapy. The therapists are trained in the brief parent training by supervisors qualified in cognitive behavior therapy during a one-day training of seven hours, in which therapists practice the parent training by roleplay and evaluate on their performance. Therapists also receive weekly supervision by these qualified supervisors when providing the brief parent training. Additionally, the supervisors provide feedback to each therapist on the audio-taped first session regarding protocol fidelity, intervention integrity, and the process of providing the training (e.g., engaging parents, didactic skills). There are no in- or exclusion criteria for clinicians in the CAU condition. To prevent contamination of the two research arms, therapists never provide both the brief behavioral parent training and CAU to parents participating in this study and are instructed not to share information about the contents of the brief training.

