### Allocation to study arms

Randomization is performed with an online generated randomization schedule [47], using blocks of six participants for each healthcare center to ensure equal allocations to both arms within and across centers. The randomization schedule is only known and administered by independent researchers who are not involved in the trial in any other way. When participants can be randomized, the independent researchers are informed at which healthcare center the parents are participating and asked to inform the responsible researchers about which condition has been randomly assigned to these parents. Randomization occurs directly after the baseline measurement (T0).

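### Therapist and centre effects enter only if a likelihood ratio test is significant, and the therapist term named cannot protect a test of change from T0

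*Protocol article*

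**What the plan says.** The Statistical analysis section lets model fit decide the hierarchy: "Depending on the fit of the models, up to four hierarchical levels will be distinguished", namely outcomes, children, therapists and centres. It names "Random intercepts at the subject level, therapist level and healthcare center level" and applies one rule to all three; the sentence ends "healthcare center level will be included only if the Likelihood Ratio Test shows a significant improvement of the model fit". The effect to be tested is stated as "The interaction between time and condition will be examined to interpret changes over time between conditions". No therapist-by-time term and no fixed centre effect is named.

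Three other sections describe the design this model has to match:

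- Study setting: "therapists never provide both the brief behavioral parent training and CAU to parents participating in this study". Therapist is therefore nested in arm.
- Allocation to study arms: randomisation follows the T0 measurement, "using blocks of six participants for each healthcare center to ensure equal allocations to both arms within and across centers".
- Sample size calculation: "Given that the data are clustered, we increased the sample size with 10" per cent, taking the total from 84 to 93.

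**The concern.** The sample size treats clustering as a fact, while the analysis lets a significance test decide whether clustering exists. A non-significant test of a variance component in about 93 families is weak evidence that the component is zero, so the gate tends to remove a real therapist effect.

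The form of the term matters as well. Families meet their trial therapist only after T0, so therapist differences in treatment effect can appear only from T1 on. An intercept shared by T0 to T3 describes something else.

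At stake is the type I error of the primary comparison. If therapist differences within an arm are left out, the standard error is too small and a difference between arms is declared too often. The Ethics and dissemination section links use of the training in practice to a finding that it is more effective.

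**Working it through.** **The plan's own figures.** For the repeated-measures within–between interaction, with f = 0.125, 2 groups, 3 measures and r = 0.60 (Sample size calculation), λ = f²·N·3/(1 − r). At N = 84, λ = 0.015625 × 84 × 3/0.40 = 9.84 with 2 and 164 degrees of freedom, and power is 0.801. Then 84 × 1.10 = 92.4, rounded up to 93. Both figures reproduce. The allowance equals a design effect of 1.10. If clustering of that size is left out of the analysis, a nominal 5% test has error 2[1 − Φ(1.96/√1.10)] = 0.062.

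**Assumed inputs.** Total variance 1, 47 and 46 children, 5 to 23 therapists per arm, and therapist variance τ² of 0.02 to 0.10 of the total. None of these therapist figures is in the article.

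**Reading A: T0 is a covariate.** A therapist intercept is then the right kind of term, and the gate decides whether it is used.

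- Chance that the 5% test (χ², 1 df) keeps a true therapist intercept in about 90 families: 3% at τ² = 0.02, 6–11% at 0.05, 13–34% at 0.10. With the mixture reference distribution it is about 6%, 10–17% and 20–42%.
- Simulation of the gated procedure (mean of T1–T3 adjusted for T0, therapist effect from T1 on, 5–15 therapists per arm, clustering in the brief arm only): the term is kept in 6–11% of trials at 0.05 and 15–29% at 0.10. Type I error is 7–9% and 7–13%.
- With clustering in both arms the term is kept more often (17–59%), but type I error is still 7–14%.
- With no therapist variance, type I error is about 5%.

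**Reading B: T0 is an outcome.** Write the outcome of child i of therapist j at time t as a mean plus therapist intercept u_j, child intercept and residual. In the difference T1 − T0, u_j cancels. A mixed-model fit to balanced data confirmed this. The standard error of the T1-by-condition term was 0.1809 with and without therapist and centre intercepts, while that of the condition main effect rose from 0.228 to 0.260.

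If therapist variance τ² arises after T0, the change in one child has variance 2(1 − 0.60) = 0.80 before the therapist part. With n children and m per therapist, an arm's mean change has variance (0.80 + mτ²)/n, but an analysis that ignores the clustering uses about (0.80 + τ²)/n. With R the ratio of true to assumed variance of the arm difference, type I error ≈ 2[1 − Φ(1.96/√R)].

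- τ² = 0.10, brief arm only, 8 therapists, m = 47/8 = 5.875. True: 1.3875/47 + 0.80/46 = 0.0469. Assumed: 0.90/47 + 0.80/46 = 0.0365. R = 1.284 and error = 0.084 (simulated 0.090).
- τ² = 0.05, brief arm only, 15 therapists, m = 3.13. R = 0.03775/0.03548 = 1.064 and error = 0.057 (simulated 0.058).
- Brief arm only, 23 therapists, m = 47/23 = 2.04. R = 1.031 at τ² = 0.05 and 1.061 at 0.10, so error is about 0.054 and 0.057.

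Simulated type I error of the T1-by-condition test, intercept-only model, 6,000 runs per cell:

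| Clustering | Therapists | τ² = 0.05 | τ² = 0.10 |
|---|---|---|---|
| Brief arm only | 8 / 10 / 15 | 0.071 / 0.065 / 0.058 | 0.090 / 0.083 / 0.070 |
| Both arms | 5 per arm, 9 families each | 0.109 | 0.167 |
| Both arms | 9 per arm, 5 families each | 0.079 | 0.117 |
| Both arms | 23 per arm, 2 families each | 0.057 | 0.077 |

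When therapist variation in change was accounted for, the error was 0.047 to 0.055 in every both-arms setting.

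**The case against.** The strongest reply is that the gate does not cause the inflation under Reading B. There the rates are the same whether or not the intercept is kept, and with a purely time-constant therapist effect (τ² = 0.10) the interaction test held 0.051. That stands. Under Reading B the problem is the form of the term. The gate does its damage under Reading A.

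A second reply is that the article does not exclude therapist-by-time terms, and that an analysis plan not shown may add them. This is fair as far as it goes. But the inclusion rule is stated in the article, not left open, and a time-constant intercept is the only therapist term it names.

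A third reply is that the sizes rest on therapist numbers and variances that the article does not give, and on balanced data although dropout is expected. This also stands. At τ² = 0.05 in the brief arm only, the error is a modest 5.8–7.1%.

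Three stronger readings are tempting, and the documents do not support them:

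- A reader might infer that the child level could be lost. The rule does cover it, but at the planned r = 0.60 the child intercept would practically always be kept.
- A reader might infer that dropping centre harms the interaction test. Centre differences that are constant over time cancel in the same way, so the effect is close to nil, and omitting a stratification factor normally errs on the conservative side. Centre belongs in the model because it is a design factor.
- A reader might infer that a therapist level makes no sense in the care-as-usual arm because families may have no clinician, or several, by T1. The article does not say so.

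**Conclusion.** The point holds and should be fixed. The article makes design-based therapist and centre effects depend on a significance test with little power, and the therapist term it names does not fit either reading safely. If T0 is a covariate, the gate usually removes a real therapist effect and leaves the comparison anti-conservative. "Usually" has a limit: with few therapists and strong clustering in both arms, the term can be kept in more than half of trials. If T0 is an outcome, the intercept is irrelevant to change since T0. The article does not settle which reading applies. The analysis section lists T1, T2 and T3 as time factors, while the sample size counts T0 as a repeated measure.

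The size depends on assumptions. Under Reading B, type I error is about 5.5–9% for therapist variance of 0.05–0.10 with 8–15 therapists in the brief arm only. It reaches 11–17% with five therapists per arm and clustering in both arms, and stays close to 5% with caseloads of about two and clustering in the brief arm only. These figures do not show that the primary test is seriously invalid. They show that its error rate is not controlled by the model as stated.

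**What to change.** Replace the gate with one pre-specified model, fixed before outcomes are analysed by arm:

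1. Say whether T0 is an outcome or a covariate.
2. Always include the child-level term, and always include centre because randomisation was stratified by it.
3. Always include a therapist effect that can act on the post-baseline occasions (therapist-by-time if T0 is an outcome). Apply it at least in the brief-training arm, and in the care-as-usual arm where a treating clinician can be identified.
4. Use a small-sample degrees-of-freedom correction, such as Kenward–Roger or Satterthwaite.
5. State a fixed order of simplification, to be used only if the model does not converge.

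The change is to wording only and needs no new outcome data. The price is slightly wider intervals if the true therapist variance is zero.

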### Objectives and hypotheses

The first objective of this study is to examine the short- and longer-term (i.e., one year) effectiveness of the brief and individually tailored behavioral parent training program with optional booster sessions compared to care as usual (CAU) on daily measured child behavioral difficulties (primary outcome) and on a range of secondary outcomes (see Outcomes). Additionally, we will explore whether a number of general demographic and clinical characteristics, parental attachment, parental psychopathology, parental reward responsivity, and reward and punishment sensitivity of the child moderate the short- and longer-term intervention effects on our primary outcome. The second objective is to investigate the cost-effectiveness of the program compared to CAU. As we assess cost-effectiveness based on measures at baseline and one year after the intervention, we can only draw conclusions about the cost-effectiveness on the longer term.

Based on our earlier work [33, 35], we hypothesize that the brief behavioral parent training with booster sessions will be more effective than CAU in reducing children’s behavioral difficulties. Consequently, we expect parents who receive the brief behavioral parent training to use less subsequent care and thus hypothesize the brief training to be more cost-effective than CAU on the longer term.

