### Outcomes

#### Primary outcome

##### Individually determined daily ratings of behavioral difficulties

The primary outcome is the mean severity of parents’ daily ratings of four selected target behaviors in specific home situations. On the adapted version of the list of target behaviors [33, 36], parents indicate whether the 29 behaviors occur daily (*yes/no*). For the behaviors scored as yes, parents rate the severity on a 5-point Likert scale ranging from 1 (*not severe*) to 5 (*extremely severe*). Behaviors scored as no are coded 0. With a researcher, parents choose four daily occurring target behaviors from this list that they prefer to work on in the training. Parents also indicate in which situation these behaviors occur, using the situations that are included in the Home Situation Questionnaire [37].

For each measurement occasion, during preferably five but at least four consecutive weekdays, short daily phone calls with parents are made to evaluate whether the four selected target behaviors occurred in the past 24 h in the selected situation (*yes/no*). Items scored as no are rated 0 and items scored as yes are rated on a 5-point Likert scale ranging from 1 (*not severe*) to 5 (*extremely severe*). This outcome is measured at all timepoints (T0-T3). For each timepoint, the average score of all four behaviors on all weekdays is used as outcome measure.

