#### Candidate moderators

In addition to the general demographic and clinical characteristics and some baseline characteristics such as the severity of behavioral problems, the following variables are included to explore whether they moderate the short- (T1) and longer-term (T2, T3) intervention effects: parental attachment as measured with the 12-item version of the Revised Experiences in Close Relationship questionnaire (ECR-R; [63, 64]),parental psychopathology as measured with the 25 items of the Strengths and Difficulties Questionnaire (SDQ) for adults [65], parental reward responsivity as measured with the 8-item Reward Responsiveness (RR) questionnaire [66], and child reward responsivity and punishment sensitivity as measured with the Punishment Sensitivity and Reward Responsivity subscales (combined 22 items) of the Sensitivity to Punishment and Sensitivity to Reward Questionnaire for Children (SPSRQ-C; [67]). All candidate moderators are measured at T0 only and reported by parents.

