### Ethics and dissemination

This study has been granted a non-WMO statement from the Medical Ethics Review Committee (METc) of the University Medical Center Groningen, meaning that the study does not meet the conditions of the Medical Research Involving Human Subjects Act. Ethics approval has been obtained from the Scientific and Ethical Review Board (VCWE) of the Vrije Universiteit (VU) Amsterdam (VCWE-2022–124). Approval to participate in this study has been obtained from all research partners. The results of this study will be submitted for publication in peer-reviewed journals. In addition, findings will be presented at scientific conferences and shared with stakeholders (e.g., parents, clinicians), for instance on our website (https://www.paint-studies.nl/) and social media channels. Regarding clinical practice, findings will be shared with parents and mental healthcare institutions, partly in collaboration with Balans (e.g., vlogs, flyers, presentations, newsletters). If the brief behavioral parent training with booster sessions is more effective than CAU in reducing children’s behavioral difficulties, the brief training can be implemented in clinical practice.

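### The 80% power stated for short-term effectiveness belongs to an omnibus test over T0, T1 and T2, not to the T1 effect that the analysis calls short-term, and no contrast is named as decisive

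*Protocol article*

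**What the plan says.** All places are in the protocol article.

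- **Statistical analysis:** "Time will be included as short-term (T1) and longer-term (T2, T3) within-subjects factors". On the test itself it says "The interaction between time and condition will be examined to interpret changes over time between conditions", without stating whether this is one omnibus test or one contrast per visit.
- **Candidate moderators** uses the same split: "moderate the short- (T1) and longer-term (T2, T3) intervention effects".
- **Sample size calculation** is based on "three repeated measures (T0, T1, T2 for short term effectiveness". Here T2 counts as short-term and T3 is absent. The inputs are d = 0.25 (f = 0.125), two groups, r = 0.60, power 0.80 and α = 0.05. The result is 42 per group, 84 in total, raised by 10% for clustering to 93.
- **Objectives and hypotheses** speaks of "short- and longer-term (i.e., one year) effectiveness".
- **Procedure:** "The second posttreatment measurement (T2) takes place six months after T1". T3 follows twelve months after T1.
- **Primary outcome** (daily ratings): "This outcome is measured at all timepoints (T0-T3"). No visit is singled out.
- **Ethics and dissemination** makes implementation depend on a result with no visit attached: "If the brief behavioral parent training with booster sessions is more effective than CAU".

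**The concern.** T2 cannot be both part of the short-term test that sized the trial and part of the longer-term effect in the analysis. The 80% is presented as power for short-term effectiveness, so a reader will attach it to the T1 effect, which is what the analysis section calls short-term. It was not calculated for that effect.

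The visits also compare different things. Under Study design, the training arm may not receive CAU until T1. After T1, CAU and booster sessions are both open to it. T1 is therefore essentially training alone against CAU, while T2 and T3 are training plus optional boosters and CAU against CAU. With no contrast named, a claim of superiority could rest on either comparison, and the choice could be made after the results are seen.

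**Working it through.** **Inputs** (Sample size calculation): f = 0.125, k = 2 groups, r = 0.60, α = 0.05. The protocol names G*Power but not the procedure. I used the repeated-measures within-between interaction with sphericity: λ = f²·N·m/(1 − r), df1 = (k − 1)(m − 1), df2 = (N − k)(m − 1), where m is the number of visits in the test.

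**1. The plan's own figure.** With m = 3 (T0, T1, T2) and N = 84, λ = 0.015625 × 84 × 3 / 0.40 = 9.84 on 2 and 164 df, and power is 80.1%. The stated 84 reproduces, and 84 × 1.10 = 92.4 rounds up to 93. The between-groups main effect over the same three visits would need 372, so it was not the test used. The pure time effect has the same formula when there are two groups, but it does not compare the arms.

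**2. Same method, other visits.**

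| Test | N | λ | df | Power |
|---|---|---|---|---|
| T0–T1 × condition (m = 2) | 84 | 6.56 | 1, 82 | 71.6% |
| T0–T1 × condition (m = 2) | 93 | 7.27 | 1, 91 | 76.0% |
| T0–T1 × condition (m = 2) | 104 | 8.13 | 1, 102 | 80.6% |
| T0–T3 × condition (m = 4) | 84 | 13.13 | 3, 246 | 86.8% |
| T0–T3 × condition (m = 4) | 93 | 14.53 | 3, 273 | 90.3% |

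The figures at 93 give full credit to the 10% that was added for clustering. On the protocol's own logic, the value at 84 is the closer one.

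**3. If d = 0.25 is a between-arm difference at T1.** This is my assumption about its meaning. In the interaction formula with m = 2, f = 0.125 puts ±0.125 SD in each of the four cells, which is a difference in change between arms of 4 × 0.125 = 0.50 SD. Check: 0.50 / (√0.80 × √(2/42)) = 2.56, and 2.56² ≈ 6.56, the λ above. With a difference of 0.25 SD instead, power ≈ Φ(0.25 / (s√(2/n)) − 1.96):

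- Change scores, s = √(2(1 − 0.60)) = 0.894: n = 42 per arm gives Φ(1.281 − 1.96) = 24.9%; n = 46.5 gives Φ(1.348 − 1.96) = 27.0%.
- Baseline adjustment, s = √(1 − 0.60²) = 0.80: n = 42 gives Φ(1.432 − 1.96) = 29.9%; n = 46.5 gives Φ(1.507 − 1.96) = 32.5%.

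**4. Error rate if each contrast were read at two-sided 5%** (assumed rule, no true effect). With change from T0 and equal correlations of 0.60, the T1 contrast and the mean-of-T2-and-T3 contrast correlate 0.40/√(0.80 × 0.60) = 0.577. The separate T1, T2 and T3 contrasts correlate 0.40/0.80 = 0.50. By simulation:

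| Contrasts | At least one p < 0.05, either direction | In favor of the training |
|---|---|---|
| One, fixed | 5% | 2.5% |
| Two (T1; T2/T3) | 8.8% | 4.4% |
| Three (T1, T2, T3) | 12.5% | 6.2% |

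With correlations from 0.375 (baseline-adjusted) to 0.60 (raw post scores), the two-sided values range from 8.8% to 9.4% for two contrasts and from 11.7% to 13.2% for three.

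**The case against.** **A reader might infer that the plan gives two or three separate chances at 5%.** The document does not say this. Alpha appears once, in the sample size, and the analysis section speaks of the interaction in the singular. A single omnibus test would keep 5%. The error rates in step 4 are therefore conditional. Only about half of each two-sided figure would be a false claim in favor of the training.

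**A reader might infer that no reading of the analysis is adequately powered.** That is too strong. If the interaction is one omnibus test over T0 to T3, the protocol's method needs only 72 participants, so 84 or 93 covers it.

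**A reader might treat the one-year wording in the objectives as a third conflicting definition.** It can equally be the length of follow-up, within which T2 and T3 both fall. I do not rely on it.

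**The exact contrast and testing order are commonly left to an analysis plan.** This is fair as far as their absence goes. It does not remove the point, because no analysis plan can agree both with the sample size section and with the moderator and analysis sections. At least one of them has to change.

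**T1 is not the obvious primary contrast.** This stands. The hypothesis concerns training with boosters. Study design opens boosters after T1, and Procedure opens them after the third session, one week before T1. T1 therefore says little about the full package, and making the T3 test depend on T1 is a debatable choice.

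**Conclusion.** The point holds for the labels and the power statement. T2 is short-term in the sample size and longer-term in the analysis and moderator sections, and the stated 80% is not the power of the T1 effect. That power is about 72% at 84 and 76% at 93 by the protocol's own method. It is roughly 25% to 33% if d = 0.25 means a between-arm difference at T1 with r = 0.60. The first pair rests on the within-between interaction that reproduces 84; the second rests on an assumed reading of d.

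The document also names no contrast that decides superiority, although the visits compare different treatment packages. A rise in the false-positive rate to about 9% or 12.5% is a possible consequence if contrasts are read separately. It is not a feature of the plan as written. The 84 is arithmetically correct for its stated inputs. This should be corrected, and it does not call the design itself into question.

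**What to change.** 1. Label T2 the same way in Candidate moderators, Sample size calculation and Statistical analysis.
2. Before outcomes are compared by arm, name one decisive time-by-condition contrast for the primary outcome and a fixed order for any second one. Three choices are workable: T1 and then T3; T3 first, because the hypothesis includes boosters; or an omnibus T0–T3 test with ordered follow-up contrasts. Say which comparison the claim of superiority then refers to.
3. Restate the power in the sample size section for that contrast at the planned number, and say whether d = 0.25 is a between-arm difference at a visit or an interaction effect size. No added enrollment is asked for.

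The cost is wording in three sections and the registry entry. If a single visit is chosen, the stated power falls below 80% (for T1, to the values above), and effects seen only at other visits become supportive. With the omnibus choice the power statement stays favorable, but a significant result does not by itself say when, or in which direction, the arms differ, so the ordered follow-up is needed.
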